#### Quality of life (QoL)

To assess quality of life we used one disease-specific questionnaire and several universal questionnaires. The standard questionnaires that were used were:

• Psoriasis Disability Index (PDI) [26,27]

• Short Form-36 (SF-36) [28,29], and

• EuroQol (EQ-5D) [30,31]

The PDI is a short questionnaire consisting of 15 questions regarding disability due to psoriasis. Answers are recorded on a seven point linear scale where '1' indicates no disability and '7' indicates maximum disability. Therefore the maximum potential PDI score is 105, with a minimum of 15 [27]. One of the generic QoL questionnaires used in the study is the SF-36, a 36-item questionnaire yielding a profile of 8 dimensions. All dimensions range in score from 0 to 100, with higher scores indicating a higher level of health status. By adding weighted combinations, the 8 scales can be combined into a physical and a mental component summary score. The EQ-5D is also a generic quality of life questionnaire. It was developed to assess the impact of a disease in terms of multi-attribute value judgements yielding one overall value judgement, a so-called utility score ranging between 0 (dead) and 1 (optimal health) [30,31]. When utility scores are plotted against time, the Area Under the Curve (AUC) reflects the Quality Adjusted Life time usually expressed in Years (QALY's). Thus QALY's will be calculated as follows: utility scores from two timepoints will be linearly interpolated (i.e. summed and devided by two). This outcome will be multiplied by the time difference. This procedure will be repeated for all parts of the curve, and the outcomes of all parts of the curve will be summed and ultimately yield an estimate of the entire AUC. In this way QALY's will be calculated for all patients, and a mean and standard error of the mean (SEM) will be determined.

Besides these standard questionnaires, we designed a brief "Burden of treatment" (BOT) questionnaire with 4 questions on the perceived burden of the UVB treatment (especially the specific burden of the treatment method and the burden of the time lost to treatment), and we developed a questionnaire on patient satisfaction. The patient satisfaction questionnaire asked about:

• waiting times,

• perceived improvement of the psoriasis lesions,

• satisfaction with the treatment as a whole,

• satisfaction with the final treatment result,

• satisfaction with the rate of improvement,

• satisfaction with the nurses' supervision,

• perceived extent of side effects,

• perceived safety of the treatment,

• perceived advantages and drawbacks of both modes of therapy, and

• preferences with regard to future UVB treatment, if necessary (home UVB phototherapy versus UVB treatment in the hospital).

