#### Cost-effectiveness

A direct comparison will be made between the effectiveness of the two therapeutic modalities and their associated cost. Incremental cost per additional patient treated successfully and costs per QALY gained will be estimated. Cost-effectiveness (CE) will be calculated for a time horizon of 12 (11–13) months after randomisation/inclusion. The quality of life (QoL) questionnaires were no longer administered after cessation of irradiation. Based on the association between clinical symptoms and QoL, the impact in terms of QoL for the remaining follow-up, i.e. up to 12 months, will be extrapolated using regression models. Subsequently, cost per QALY can be calculated. In case the difference in effectiveness is less than 15%, we will consider this as equal effectiveness and will limit the economic evaluation to a cost minimisation analysis.

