**Figure 1 F1:**
[figure not shown]
**Timetable**. Schematic representation of successive time points for data collection, reported for all outcome measures and questionnaires. * 23 irradiations: outcome measurement was planned at approximately 23 irradiations, with a minimum of 20 and a maximum of 26 irradiations. ** End of therapy: measurement was planned at the end of the treatment. When more than 46 irradiations were needed, measurement was planned at 46 irradiations. *** Follow-up: Starting at the end of the therapy (or at the 46^th ^irradiation, see **), follow-up measurements were planned every 2 months, for up to 1 year after the last irradiation.

Immediately after this first visit, patients were randomised using the baseline data (information on the recruiting hospital and any previous experience of the patient with UV therapy were used to determine the randomisation strata). Both patient and attending dermatologist were informed about the type of treatment assigned, and the treatment was started accordingly. When (sometimes after a waiting period) the therapy was started, the patients did a SAPASI-assessment and began using the study diary. At approximately 23 (20–26) UVB treatments ànd at the end of the therapy (or 46 treatments) the patients received a series of questionnaires at home. Visits to the previously mentioned research nurse were scheduled for the same time points. Throughout the whole trial, the independent research nurse was not informed about the randomisation results and therefore remained blinded.

For all UVB therapies lasting longer than 46 treatments, a cutoff point of maximally 46 treatments was used to establish effectiveness. The choice of 46 as the maximum number of treatments was derived from unpublished data from the home care organisations about the treatment duration of their patients.

At the end of the therapy (or 46 treatments), 105 patients were followed for 12 more months to monitor long term effectiveness and cost. The patients received a short questionnaire at home every 2 months and returned this questionnaire by mail. At the end of the follow-up, information on medication use during the trial period was retrieved retrospectively for each patient from his/her pharmacist.

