### Statistical analysis

All data will be analysed according to the intention to treat principle, meaning all included patients will be analysed according to the group they were randomised to. This includes patients who dropped out or changed therapy. The statistical methods that will be used are chosen in accordance with the type of data that is available. For continuous data differences and their 95% Confidence Intervals (95% CIs) will be presented. In case of binary outcomes, differences in proportion with 95% CIs will be calculated. Whether randomisation was successful will be determined by assessing comparability of baseline characteristics. No formal statistical tests are foreseen. In the event apparent differences are noted, a multivariate analysis will be performed to adjust for potential confounding.

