#### Quality of life (QoL)

Continuous sum-scores of the QoL questionnaires will be compared by calculating differences in QoL and their 95% CIs. Changes in QoL will also be compared across groups.

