#### Cost-effectiveness

Initially the trial estimate of the incremental cost per additional patient with successful outcome will be assessed. Similarly, the cost per QALY gained will be estimated. To assess uncertainty with regard to incremental cost-effectiveness a standard bootstrap technique will be applied [35]. The trial data will be randomly sampled with replacement from the original dataset 1000 times. For each bootstrap sample the incremental costs and effects will be calculated and plotted (costs on the y-axis and effects on the x-axis). Thus an integrated presentation of the mutually dependent cost and effect differences is obtained that may be interpreted as a direct reflection of the uncertainty, i.e. a two dimensial dispersion, with regard to the incremental cost-effectiveness ratio. Using this so-called CEA Plane (Cost-effectiveness Analysis Plane), an inference regarding the likelihood of one treatment being more cost-effective than the other can be made [36].

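### The QALY increment and its bootstrap have no prespecified adjustment for baseline EQ-5D; the general rule adjusts only when a baseline difference looks apparent and is not tied to either

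*Protocol article*

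**What the plan says.** Four parts of the protocol article bear on this.

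- **Construction of the QALY** (Outcome assessment, Quality of life): "utility scores from two timepoints will be linearly interpolated (i.e. summed and devided by two). This outcome will be multiplied by the time difference". The pieces are summed, and "In this way QALY's will be calculated for all patients, and a mean and standard error of the mean (SEM) will be determined".
- **Uncertainty** (Statistical analysis, Cost-effectiveness): the data are resampled 1000 times, and "For each bootstrap sample the incremental costs and effects will be calculated and plotted (costs on the y-axis and effects on the x-axis". No covariate is mentioned.
- **Balance at randomisation** (Measurement planning; also Randomisation procedure): "information on the recruiting hospital and any previous experience of the patient with UV therapy were used to determine the randomisation strata". Utility is not a balancing factor.
- **General adjustment rule** (opening paragraph of Statistical analysis): "Whether randomisation was successful will be determined by assessing comparability of baseline characteristics. No formal statistical tests are foreseen". Then: "In the event apparent differences are noted, a multivariate analysis will be performed to adjust for potential confounding".

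Two further statements limit the reach of the point. If the effectiveness difference is under 15%, "we will consider this as equal effectiveness and will limit the economic evaluation to a cost minimisation analysis" (Outcome assessment, Cost-effectiveness). For the questionnaire scores, "Changes in QoL will also be compared across groups" (Statistical analysis, Quality of life); this concerns sum-scores, not the QALY.

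**The concern.** The starting utility is part of the area that is being compared, and later utilities are normally correlated with it. A difference between arms that existed before treatment therefore enters the QALY difference twice: directly through the first segment, and indirectly through the later measurements.

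The general rule acts only if someone looking at the baseline table judges a difference to be apparent. With no threshold, a moderate utility imbalance may pass unremarked. If the rule is triggered, the text does not say that the adjustment reaches the QALY or is repeated inside the bootstrap. Deciding on adjustment after seeing the baseline data also makes the estimator depend on the data, and gives up the gain in precision whenever the arms look alike.

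The increment at stake may be small, because the Sample size section expects similar effectiveness. A shift of one or two hundredths of a QALY could then change its sign, or the cost per QALY, substantially.

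**Working it through.** The plan states no QALY difference, utility SD or correlation, so it has no figure of its own to reproduce here.

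**Inputs from the article.** 196 patients, 98 per arm (Table 3). 105 were followed after treatment, about 52 per arm if split equally (52.5 is used below). The horizon is 12 months. EQ-5D was measured only up to the end of treatment, and the rest is extrapolated.

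**Assumptions.** Utility SD 0.20. Equal correlation ρ of 0.3, 0.5 or 0.7 between any two time points. A baseline EQ-5D exists. EQ-5D falls at weeks 0, 12, 20, 52 (schedule A) or 0, 8, 14, 52 (schedule B), with week 52 extrapolated. Visits follow irradiation counts, so true times vary: 23 irradiations take 23/3 to 23/2 = 7.7 to 11.5 weeks at the hospital frequency, and 23/4 to 23/3 = 5.8 to 7.7 weeks at the home frequency.

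**Trapezoid weights (years).**
- A: 0.1154, 0.1923, 0.3846, 0.3077; sum 1; sum of squares 0.2929.
- B: 0.0769, 0.1346, 0.4231, 0.3654; sum 1; sum of squares 0.3365.

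**Formulas**, with w₀ the baseline weight:
- slope of QALY on baseline: b = w₀ + ρ(1 − w₀)
- K = ρ + (1 − ρ)Σw², so Var(QALY) = SD² × K
- share of variance removed by adjustment: R² = b²/K
- SE of the baseline difference = SD × √(2/n)
- shift from a one-SE imbalance = b × that SE

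**Worked case (A, ρ = 0.5, n = 98).** b = 0.1154 + 0.5 × 0.8846 = 0.558. K = 0.5 + 0.5 × 0.2929 = 0.6465. R² = 0.311/0.6465 = 0.48. Baseline SE = 0.20 × √(2/98) = 0.0286. Shift = 0.558 × 0.0286 = 0.016. SE of the QALY difference = √(2 × 0.04 × 0.6465/98) = 0.0230, falling to 0.0230 × √0.519 = 0.0165.

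| Case | ρ | b | One-SE shift | Variance cut |
|---|---|---|---|---|
| A, 98 per arm (baseline SE 0.0286) | 0.3 | 0.381 | 0.011 | 29% |
| | 0.5 | 0.558 | 0.016 | 48% |
| | 0.7 | 0.735 | 0.021 | 69% |
| B, 52.5 per arm (baseline SE 0.0390) | 0.3 | 0.354 | 0.014 | 23% |
| | 0.5 | 0.538 | 0.021 | 43% |
| | 0.7 | 0.723 | 0.028 | 65% |

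**SD.** The shift is proportional to it: 0.012 at SD 0.15 and 0.020 at SD 0.25 (A, ρ = 0.5, 98 per arm). The variance cut does not depend on it.

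**Would the rule notice?** A one-SE imbalance is 0.0286/0.20 = 0.14 SD with 98 per arm, and 0.0390/0.20 = 0.20 SD with 52.5. Neither would stand out in a baseline table.

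**Weak link with the extrapolated months.** Take A with ρ = 0.5, but no correlation between baseline and week 52. Then b = 0.1154 + 0.5 × (0.1923 + 0.3846) = 0.404, and K = 0.6465 − 2 × 0.1154 × 0.3077 × 0.5 = 0.611. R² = 0.163/0.611 = 0.27, and the shift is 0.404 × 0.0286 = 0.012. The gain falls from 48% to 27% but remains.

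**The case against.** A reader might infer that the plan makes no provision for baseline differences. It does: the general rule opens a section that covers all data, and it could be applied to EQ-5D. What can be criticised is its trigger and its missing link to the QALY and the bootstrap.

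A reader might also infer that the QALY estimate is biased or the bootstrap faulty. Neither follows. Under randomisation a chance imbalance is sampling error, and both the SEM and the bootstrap spread already allow for it. The loss is in precision, and in how far one realised estimate may lie from the truth.

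Nor does the whole cost-effectiveness question hang on this. Cost per successfully treated patient is estimated first and involves no baseline utility. If effectiveness differs by less than 15%, which the design expects, the evaluation is limited to cost minimisation and no cost per QALY may be reported.

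Finally, covariates are often left to an analysis plan, which is not shown and may name this one. That has weight, but the article does set out the QALY calculation, the bootstrap and an adjustment rule in some detail, and that stated rule is the weaker choice. A baseline EQ-5D is itself inferred: the timetable figure is not shown, though baseline data were recorded and the area needs a starting value.

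**Conclusion.** The point holds as a matter of efficiency and prespecification in a secondary analysis. As written, the QALY increment is adjusted for baseline utility only if an imbalance happens to look apparent, and nothing carries that adjustment into the bootstrap. With an assumed utility SD of 0.20 and correlations of 0.3 to 0.7, an unremarkable one-SE imbalance moves the 12-month QALY difference by about 0.011 to 0.021 (98 per arm) or 0.014 to 0.028 (about 52 per arm). Always adjusting would cut its variance by about 23% to 69%, and by less where the extrapolated period is weakly related to baseline. These sizes rest on assumed SD, correlations and visit times. The point matters only if the cost-per-QALY analysis is run. It does not touch the PASI comparison or the comparisons of questionnaire scores.

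**What to change.** State that, whatever baseline imbalance is observed, the incremental QALY is estimated by regressing each patient's QALY on randomised arm and baseline EQ-5D utility. Refit that regression in each of the 1000 bootstrap samples, so that the effects on the cost-effectiveness plane and the cost per QALY use the adjusted difference. Show the unadjusted difference as a secondary figure. Apply this wherever the QALY analysis is not replaced by cost minimisation.

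The cost is a sentence or two in the plan, one degree of freedom and one simple regression per bootstrap sample. No new data are needed, provided EQ-5D was collected at baseline.

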#### Costs

Estimation of costs will be based partially on the actual cost of the resources used, for instance the rental price of home UVB light panels, the cost of using hospital equipment, and travel expenses among others. Some indirect costs-such as the loss of work time due to decreased efficiency or absenteeism-were assessed using the "Health and Labour Questionnaire" [32], a general introductory questionnaire and the previously mentioned diary. These two questionnaires will supply information on time lost or expenses incurred for the treatment of the psoriasis, for instance the cost of transportation to a dermatologist or general practitioner. The diary on the other hand provides information on the frequency of these types of expenses during the treatment period. From the patients' pharmacists we obtained data on the use of medications and their prices. The friction cost method [33] will be applied to assess the losses to society due to sick leave.

#### Cost-effectiveness

A direct comparison will be made between the effectiveness of the two therapeutic modalities and their associated cost. Incremental cost per additional patient treated successfully and costs per QALY gained will be estimated. Cost-effectiveness (CE) will be calculated for a time horizon of 12 (11–13) months after randomisation/inclusion. The quality of life (QoL) questionnaires were no longer administered after cessation of irradiation. Based on the association between clinical symptoms and QoL, the impact in terms of QoL for the remaining follow-up, i.e. up to 12 months, will be extrapolated using regression models. Subsequently, cost per QALY can be calculated. In case the difference in effectiveness is less than 15%, we will consider this as equal effectiveness and will limit the economic evaluation to a cost minimisation analysis.

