In an earlier study we listed all known publications and studies on home UVB phototherapy, and conducted a survey among dermatologists [14]. We found that in the Netherlands home UVB is currently prescribed to approximately 5% of the UVB-treated patients, with some dermatologists prescribing it in 100% of the cases. We also demonstrated that there is no firm evidence that would either support or dissuade from prescribing home UVB phototherapy. Glaringly absent is any randomised research in this area. This lack of research has resulted in ongoing discussions and the dissemination of personal, non-evidence based opinions, especially with regard to issues like effectiveness, side effects and cost [14]. Thus, in general, home UVB phototherapy remains a debated treatment. We concluded that only randomised research on home UVB phototherapy as compared to UVB treatment in an outpatient setting could resolve the issue [14].

In this paper, we describe a randomised pragmatic trial that we are currently conducting, a national trial on home UVB phototherapy for psoriasis. The Dutch acronym for this trial is PLUTO (Psoriasis: Landelijk UVB Thuisbelichtings Onderzoek). The trial is designed to evaluate the impact of home UVB phototherapy versus conventional outpatient UVB phototherapy on effectiveness, quality of life and cost-effectiveness. The focus is on narrowband UVB treatment (TL-01 lamps). The study tests the hypothesis that home UVB phototherapy is as effective as outpatient UVB phototherapy. We further expect a better quality of life when patients are treated at home, and we hypothesize that home treatment will have similar or reduced total costs. This article presents the design of this trial.

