### Sample size

The sample size could not be calculated on the basis of presumed differences in effectiveness as there is no clear data available on the possible differences in treatment effects. However, based on the data available from a 1993 pilot study [16] and recent experience with home UVB phototherapy, we in fact expected the effectiveness of both therapies to be similar. The sample size was therefore calculated in accordance with a negative trial approach [17]. We considered a 50% or greater improvement in the psoriasis severity from baseline to be a relevant clinical response. A systematic review by Spuls et al. indicates that approximately 85% of the patients treated with UVB show at least a 50% improvement in their psoriasis [18]. Thus, with N = 90 per per treatment group and at α = 0.05 and β = 0.20 (power 80%), we would be able to show a difference in effectiveness of 15% or more; i.e., a reduction in effectiveness from 85% to 70% or less should be distinguishable. To allow for missing data and losses to follow-up (i.e. withdrawals, incomplete case register forms) we aimed at 100 patients per group, 200 in total. To obtain accurate estimates of the cumulative costs of UVB treatment a consecutive sample of 100 patients (50 per group) was considered to be sufficient, because little variation was expected in treatment duration, number of UVB irradiations, and use of concomitant medication.

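### Equal effectiveness, and with it a switch to cost minimisation only, is declared on a difference below 15% with no confidence limit, at odds with the sample size and the planned cost-effectiveness bootstrap

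*Protocol article*

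**What the plan says.** Four places in the protocol article bear on this.

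- **Outcome assessment, Cost-effectiveness.** The rule is "In case the difference in effectiveness is less than 15%, we will consider this as equal effectiveness". Its consequence is that the investigators "will limit the economic evaluation to a cost minimisation analysis". No confidence limit, test, direction, outcome measure or time point is given.
- **Sample size.** The trial was sized by a negative-trial approach because the two treatments were expected to perform alike. The response is defined: "We considered a 50% or greater improvement in the psoriasis severity from baseline to be a relevant clinical response". The reference rate is that "approximately 85% of the patients treated with UVB show at least a 50% improvement in their psoriasis". With 90 per group, α = 0.05 and 80% power, the article says "a reduction in effectiveness from 85% to 70% or less should be distinguishable".
- **Statistical analysis.** "All data will be analysed according to the intention to treat principle". Differences in proportions, and differences in PASI and SAPASI scores, are to be presented with 95% CIs. Nothing links these intervals to the 15% rule.
- **Statistical analysis, Cost-effectiveness.** "Initially the trial estimate of the incremental cost per additional patient with successful outcome will be assessed". Cost per QALY and 1000 bootstrap samples on a cost-effectiveness plane follow. This section does not mention that the analysis might be dropped.

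The Background states the aim that the rule echoes: "The study tests the hypothesis that home UVB phototherapy is as effective as outpatient UVB phototherapy".

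**The concern.** The rule compares an estimate with 15% and ignores its uncertainty. When the true loss is 15 points, the observed loss falls on either side of 15 with roughly equal probability, whatever the sample size. The Sample size section says a loss of that size should be distinguishable, yet the rule would label it equal about half the time.

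What is at stake is the economic result. Cost minimisation sets the effect difference to zero. If home treatment proved cheaper and somewhat less effective, the lost benefit would vanish from the comparison, and the incremental cost per successfully treated patient and per QALY promised in the objectives would not be reported.

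**Working it through.** **Inputs.** Outpatient response 85%, margin 15 points, α = 0.05, power 80%, 90 per group (Sample size). 98 per arm randomised (Table 3). 105 patients followed for 12 months (Results), so about 52 per arm if split evenly, which is an assumption. Response is taken as at least 50% improvement, also an assumption for the rule.

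**Step 1: the plan's own figure.** For a true difference of zero, with the upper limit of the two-sided 95% CI for the loss required to lie below 15 points:

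n = (1.96 + 0.8416)² × 2 × 0.85 × 0.15 / 0.15² = 7.849 × 0.255 / 0.0225 = 88.95, so 89 per group.

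Power at 90 is 80.5%. This reproduces the stated 90. The alternatives fit less well:

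- superiority test of 85% v 70%: 121 per group two-sided, 95 one-sided at 0.05
- non-inferiority at one-sided 0.05: 71
- two-sided equivalence: 120 at 0.025 per side, 98 at 0.05 per side

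**Step 2: how often each rule declares equality.** Two independent binomials were enumerated exactly, with outpatient at 85%. The written rule is P(observed loss < 0.15). The CI rule is P(d + 1.96 × SE < 0.15), where d is the observed loss, SE² = [p₁(1−p₁) + p₂(1−p₂)]/n, and p₁ and p₂ are the observed rates.

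| Home truly | Written rule, n=90 | n=98 | n=52 | CI rule, n=90 | n=98 |
|---|---|---|---|---|---|
| 85% | 0.998 | 0.998 | 0.98 | 0.804 | 0.836 |
| 75% | 0.80 | 0.80 | 0.72 | 0.137 | 0.145 |
| 70% | 0.50 | 0.49 | 0.47 | 0.026 | 0.026 |
| 65% | 0.21 | 0.19 | 0.25 | 0.003 | 0.003 |

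Reading the rule as an absolute difference leaves the 70% row unchanged to two decimals. With 100 per arm a loss of exactly 15 points can occur; the 70% entry is then 0.47 if that result does not count as equal and 0.53 if it does.

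**Step 3: one result.** Take illustrative observed rates of 85% and 71% with 98 per arm. SE = √[(0.1275 + 0.2059)/98] = 0.0583. The 95% CI for the loss is 14 ± 1.96 × 5.83 = 2.6 to 25.4 points. It excludes zero and reaches well beyond 15, yet the rule says equal. Under the CI rule, with outpatient observed at 85%, the observed loss could be at most about 4 points.

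**Step 4: the two cost-effectiveness paragraphs.** Under Outcome assessment, a difference below 15% reduces the evaluation to cost minimisation. Under Statistical analysis, the incremental ratios and the bootstrap are planned with no such condition. For the result in step 3, the first paragraph cancels the bootstrap and the second requires it.

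**The case against.** **Scope.** A reader might infer that the trial's main conclusion hangs on this rule. The article does not say so. The sentence sits under cost-effectiveness and its only stated consequence is economic. The clinical comparison is planned separately with 95% CIs, so in the step 3 example the interval would be published and the loss would be visible. This stands and limits the point. What remains is that this is the document's only criterion for equality, and that the interval does not enter it.

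**Analysis set.** A reader might also infer that intention to treat makes an equality claim too easy, and that a per-protocol analysis is required. The documents do not support that. The design compares whole strategies and permits treatment changes after randomisation. Of the seven who never started, four had improved while waiting, three of them in the home arm, so excluding them would depend on outcome.

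The dilution is also small. Results gives 91 outpatient and 93 home patients treated as allocated, 4 and 1 switchers, and 3 and 4 never-starters. With true rates of 85% and 70%, and an assumed common response r in never-starters, the difference is [(91×0.85 + 4×0.70 + 3r) − (93×0.70 + 1×0.85 + 4r)]/98 = (14.20 − r)/98. That is 14.5 points at r = 0 and 13.5 at r = 1.

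**Reading of the rule.** The words say only the difference, not the observed difference, and name no measure. The Sample size section also speaks of showing a difference, which sounds like a superiority test. These are fair cautions. But the rule can only be applied to trial data, the responder proportion is the only outcome to which the article attaches 15%, and 90 per group agrees best with the CI-based design.

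**Conclusion.** The point holds as a defect in the gate that chooses the form of the economic evaluation. As written, the gate calls a true 85% v 70% equal with probability 0.47 to 0.50 for 52 to 98 per arm, against about 0.026 if the 95% CI must exclude a 15-point loss. It is inconsistent with the article's own sizing and with its unconditional bootstrap plan.

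The figures assume that the rule is applied to the observed difference in the proportion with at least 50% improvement, and that the outpatient rate is 85%. The finding of about one half barely depends on the number evaluable. Neither the sample size nor the choice of intention to treat is at fault.

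**What to change.** Replace the rule with: effectiveness will be considered equal only if the two-sided 95% CI for home minus outpatient response (at least 50% improvement, by intention to treat) excludes a reduction of 15 percentage points or more.

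Reconcile the two cost-effectiveness paragraphs by running the joint cost-effect bootstrap in every case and showing cost minimisation only as a secondary scenario.

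The cost is wording: the intervals and the bootstrap are already planned. With 90 to 98 evaluable per arm, the chance of concluding equality when both arms are truly 85% is 80% to 84%, which is what the trial was sized for. That holds for the full effectiveness comparison. In the 105-patient follow-up sample (52 per arm) it would be 0.58, so the criterion should be applied to the full comparison.

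The downside is that equality becomes harder to claim: observed losses between about 4 and 15 points would no longer qualify.

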## Methods

### Objective

The aim of this study is to compare home UVB (TL-01) phototherapy with the current outpatient UVB (TL-01) phototherapy for patients with psoriasis. This objective was specified by the following research questions. Compared to outpatient UVB phototherapy:

1. Is home UVB phototherapy for patients with psoriasis equally effective?

2. Does home UVB phototherapy yield a better quality of life?

3. Are costs for home UVB phototherapy higher, lower or similar?

4. Is home UVB phototherapy cost-effective?

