#### Effectiveness

We assessed the effectiveness of both treatments using the Psoriasis Area and Severity Index (PASI) [21] and the Self-Administered PASI (SAPASI) [22]. Both indices evaluate the severity of the psoriatic lesions ànd the area of psoriatic involvement. Their scores vary from 0.0 (no lesions at all) to 72.0 (complete erythroderma of the severest possible degree) [21]. An independent and blinded research nurse administered the PASI during several patient visits to the outpatient clinic. The SAPASI was easier to collect using a questionnaire and was used as an equivalent of the PASI as well as an indicator of the patient's own impression of the extent of the psoriasis lesions [22,23] Both the PASI and the SAPASI were assessed for the whole body, including the lower legs and the scalp. We also determined skin type according to Fitzpatrick's classification of skin phototypes [24,25] and collected data on concomitant use of medication, side effects, demographics and past medical history.

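### The switch to cost minimisation tests clinical effectiveness only, so in the scenario the trial expects it would usually replace cost per QALY and leave research question 4 without a joint cost-QALY result

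*Protocol article*

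**What the plan says.** All references are to the protocol article.

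- **The rule.** Methods, Outcome assessment, Cost-effectiveness first announces two ratios, cost per additional successfully treated patient and cost per QALY. It then adds that, for a difference in effectiveness below 15%, "we will consider this as equal effectiveness and will limit the economic evaluation to a cost minimisation analysis".
- **What effectiveness means.** The Effectiveness section under Outcome assessment says "We assessed the effectiveness of both treatments using the Psoriasis Area and Severity Index (PASI") and its self-administered version. Sample size adds the responder definition: "We considered a 50% or greater improvement in the psoriasis severity from baseline to be a relevant clinical response". The 15% there is the drop from 85% to 70% responders.
- **What the trial expects.** Background and Sample size expect similar effectiveness. Background adds: "We further expect a better quality of life when patients are treated at home". Objective makes this research question 2, "Does home UVB phototherapy yield a better quality of life"; cost-effectiveness is question 4.
- **The analysis text.** Statistical analysis, Cost-effectiveness states "Similarly, the cost per QALY gained will be estimated", followed by 1000 bootstrap samples and the cost-effectiveness plane. It does not mention the 15% condition. The Discussion also announces a cost-effectiveness analysis without condition.

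**The concern.** Cost minimisation compares costs alone. It is justified when the outcomes that would otherwise be valued can be taken as equal. Here the check for equality covers one outcome, clinical severity. Quality of life has its own instruments, its own research question and its own analysis, and the investigators expect it to differ between the arms. Even a clinical difference known to be exactly zero would not show that QALYs are equal.

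So the rule takes out the QALY comparison in the very scenario the trial was set up to examine. At stake is research question 4. If home treatment costs somewhat more and quality of life is better, or costs less and quality of life is worse, a cost-only evaluation cannot weigh one against the other. Because the two Cost-effectiveness sections are not aligned, it is also open which analysis answers question 4, and that choice could be made after results are known.

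**Working it through.** **Inputs.** Response 85%, margin 15 points, 90 per group, α = 0.05, power 80% (Sample size); 98 per arm randomised (Table 3). I assume that the 15% in the economic rule is the responder difference of the Sample size section; the rule does not say so.

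**1. The plan's own figure.** Non-inferiority with 85% in both arms, margin 0.15, one-sided 0.025, power 80%:

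n = (1.960 + 0.842)² × 2 × 0.85 × 0.15 / 0.15² = 7.85 × 0.255 / 0.0225 ≈ 89 per group, against 90 stated. It reproduces. A two-sided superiority calculation for 85% against 70% gives 121, so 90 fits the non-inferiority reading.

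**2. How often the switch applies if the arms respond equally.**

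SE = √(2 × 0.85 × 0.15 / 90) = 0.0532; 0.15 / 0.0532 = 2.82.

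| Reading of the 15% rule | Calculation (90 per group) | 90 per group | 98 per group |
|---|---|---|---|
| Observed difference within 15 points | P(\|Z\| < 2.82); exact binomial agrees | 99.5% | 99.6% |
| 95% CI excludes a 15-point loss | Φ(2.82 − 1.96) = Φ(0.86) | 80% | 84% |
| 95% CI wholly within ±15 points | 2 × Φ(0.86) − 1 | 61% | 67% |

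For 98 per group, SE = √(0.255 / 98) = 0.0510 and 0.15 / 0.0510 = 2.94; the CI rows use Φ(2.94 − 1.96) = Φ(0.98), and the first row is the exact binomial value.

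**3. If home response is somewhat lower.** On the point-estimate reading with 90 per group (exact binomial), the switch still applies in about 96% of trials at a true home rate of 80%, and about 80% at a true home rate of 75%.

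**4. Does quality of life enter any of these?** No. The probabilities are the same whatever the EQ-5D shows, because the rule does not refer to it.

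**5. The two sections side by side.** Outcome assessment: cost per QALY only if effectiveness differs by 15% or more. Statistical analysis: cost per QALY and the bootstrap plane, no condition. Both cannot be followed when the clinical difference is small.

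**The case against.** The strongest reply has four parts.

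- **The condition may only be stated once.** The specific rule could govern and the Statistical analysis section simply not repeat it, so there would be no contradiction. That is possible, but it makes the main problem certain: the QALY analysis is then dropped without any look at QALYs. If the unconditional text governs, the switch has no effect. Either way the text needs settling.
- **The switch is not certain to apply.** A reader might infer from the 99.5% that cost per QALY is almost always dropped. That figure holds only on the point-estimate reading. Because the article reports effectiveness with 95% CIs, a CI reading is at least as natural, and it gives about 80% or 61%. This stands; the supportable word is usually.
- **Quality of life is not lost.** A reader might infer that a worse quality of life would be hidden, or that the rule names a preferred arm. Neither is supported. Statistical analysis, Quality of life compares scores and changes between groups, cost differences are reported with CIs, and the document has no rule for declaring a preferred arm. What goes missing is the joint summary.
- **The QALY difference may be small.** The EQ-5D stops at the end of treatment and later quality of life is modelled from clinical symptoms. With equal symptoms, any QALY gain would lie largely in the treatment period. The expected benefit might also appear on the other questionnaires and not on the EQ-5D. This stands as a caution on size. It does not justify assuming in advance that the difference is zero.

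**Conclusion.** The rule is wrong as written. It lets equality on clinical response stand in for equality on everything the economic evaluation would value, although the trial expects quality of life to differ. Under equal 85% response with 90 per group it applies in about 61% to 99.5% of trials, depending on a reading of the 15% that the article leaves open. In every reading this is more often than not.

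The consequence is confined to research question 4, which would lack a joint cost-QALY result. The effectiveness comparison, the randomisation and the separate quality-of-life comparison are untouched, and no data are lost. It would be tempting to put a money value on what is left out. The document gives neither a utility difference nor a value per QALY, so no such figure is supported. The conclusion rests on two assumptions: that the 15% is the responder difference, and that both arms respond at 85%.

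**What to change.** Remove the switch from the Cost-effectiveness section under Outcome assessment. State that the cost-per-QALY analysis and the bootstrap cost-effectiveness plane of the Statistical analysis section are carried out whatever the clinical difference. Show the cost difference with its CI alongside as a secondary result. This also reconciles the two sections, and the open reading of the 15% no longer affects the economic evaluation.

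The change is one sentence. EQ-5D data during treatment, the QALY calculation and the bootstrap are already in the plan, so no new data are needed. The price is a less simple economic message than a cost comparison alone. A lighter alternative, keeping the switch but also requiring equality on QALYs, would meet the main objection, but the criteria for both equalities would then have to be defined.
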